#### **Secondary Analysis Depression and Anxiety Score:**

The subjects are classified as screen positive if he/she fulfil either one of below mentioned three category:-

1. Depression Sore  $\geq 10$
2. Anxiety Score  $\geq 10$
3. Suicidal tendency Score  $\geq 1$

The depression and anxiety will be categorized as Normal if their total score is in between 0-

4. The score in between 5-9 will be classify as Mild. The score in between 10-14 will be classify as moderated. The score of 15 or greater will be treated as severe.

The Anxiety and Depression score will be categorized by their severity. The count and percentage for depression and Anxiety at baseline and post baseline will be presented by severity. A separate table will be presented for depression score  $\geq 10$  and anxiety score  $\geq 10$  at baseline and post intervention.

A separated table will be provides for the only screen positive subjects with the count and percentage of the symptoms which lead them to be screen positive.

The summary statistics (N, Mean, STD, Min and Max) for anxiety and depression score by visit will be presented. The difference in score between baseline and post intervention will be summarized in similar fashion. The mean difference in score between baseline and post intervention will be statistically analyzed by paired t-test. The p-value from the analysis will be presented in same table.

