**Smart mental health Visit schedule and analysis for visit:**

The study will be reported in mainly 2 category:-

1. Baseline (As applicable, this will includes ASHA screening data available in in ASHA Screening 1 and ASHA follow up 1. OR Baseline data collected by study interviewers)
2. Post Intervention (collected by study interviewers)

All the subject at post intervention are screen positive subjects. They were screened positive either at Baseline by study interviewers or at Intervention visits (ASHA screening 1 and ASHA follow-up 1) by ASHA. All the screen positive subjects were followed by ASHAs which is available in the ASHA follow up data.

Unless otherwise stated, the summary tables will be presented under 2 category:-

1. Baseline
2. Post Intervention

The difference between Baseline and Post Intervention will provide effect of intervention.

Apart from the Post Intervention data, post stigma data was also collected. At the time of creating derived data for post Intervention, both data (Post Intervention and post stigma) are appended together and created a single data set. A flag variable containing record ("Post Intervention" & "post stigma") was created was created in derived data set to identify such records.

Unless otherwise stated, all the analysis will be presented for all the subject who are screen positive by ASHA.

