**Smart mental health Final Statistical Analysis plan Primary Analysis:**

The primary objective of the study is:-

To see the difference in anxiety and depression score and health service utilization among the mental health screen positive subject post intervention.

The screen positive subjects at baseline will be looked for their past history for mental health service utilization. The subjects who responded "Yes" against question number 56 "Did you get treated for that mental disorder?" are proportion of subject at baseline who used mental health service.

At post intervention, the number of subjects used health service can be taken from Doctors follow-up data.

The count and percentage will be provided for the subjects who are screen positive for utilization of health services. Proportion of mental health service utilization at baseline and post intervention among the screen positive subject will be statistically analyze by McNemar test. The P-value for comparison of will be presented in same table.

A separate table will be provided for subjects screen positive subjects who actually visited doctor for their treatment at time of intervention. The count and percent by visit will be provided for this.

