#### **Case control Analysis of Primary objective:**

All the subjects screened positive by ASHA are case here. The subjects who mental health are screen negative by ASHA, but screen positive by interviewer are kind of control in this study setup. Such subjects will be called as control.

A case control analysis will be performed to assess the difference in anxiety and depression score and mental health service utilization.

For this difference in anxiety and depression score for individual subjects will be computed from ASHA screen data and post intervention data. Further this difference in case and control will be statistically analyses by 2 independent sample t-test. Difference of difference in score between case and control along with p-value will be presented.

For health service utilization between cases and control, Count along with percent and Chi- square P-value will be presented.

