**Proportion of subject used health services**

| Category | Baseline | Post Intervention | P-Value |
|-----------------|-----------------|--------------------------|----------------|
| Case*           | xxxx            | xxxx                     | 0.xxx          |
| Control**       | xxxx            | xxxx                     |                |

*Health Service used: At baseline: Response from the question “Did you get treated for that mental disorder?”*

*At Post Intervention: Response from the question “Did you get treated for your mental health condition as indicated by ASHA/Interviewer?”*

*\* Case: The subjects who are screen positive by ASHA.*

*\*\* Control: The subjects who are screened negative by ASHA but positive by study interviewer.*

*P-Value is calculated based chi-square independent sample test of proportion.*

Table 17: Subject Referrals during ASHA screening

| Screened by |                                                                                                            | (N*=xxxxxx)
n(%) |
|-------------|------------------------------------------------------------------------------------------------------------|---------------------|
| ASHA        | Out of those Screened by ASHA Proportion of subject referred to the PHC doctor                             | xxxx (xx.xx)        |
|             | Out of those referred to PHC doctors Proportion of subjects actually visited doctors                       | xxxx (xx.xx)        |
|             | Out of those visited doctors Proportion of subjects appropriately prescribed anti-depressant or anxiolytic | xxxx (xx.xx)        |
|             | Out of those visited doctors Proportion of subjects appropriately referred by the PHC doctor for more      | xxxx (xx.xx)        |

\*N= overall population screened by ASHAs.

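### The before-after tests on the primary endpoints ignore clustering by ASHA and PHC, so any within-cluster correlation of change makes their p-values too low

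*SAP*

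**What the plan says.** The primary objective, under Primary Analysis, is "To see the difference in anxiety and depression score and health service utilization among the mental health screen positive subject post intervention". The tests named for it are:

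- **Score change, before to after:** "The mean difference in score between baseline and post intervention will be statistically analyzed by paired t-test". This stands under the Secondary Analysis heading, but it is the only before-after test the SAP names for the scores in the primary objective.
- **Service use, before to after:** the two proportions "will be statistically analyze by McNemar test". The footnote to Table 15 repeats this.
- **Score change, cases against controls:** "this difference in case and control will be statistically analyses by 2 independent sample t-test".
- **Service use, cases against controls:** "For health service utilization between cases and control, Count along with percent and Chi- square P-value will be presented".

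No mixed model, GEE, cluster-robust variance, or term for ASHA, PHC or village appears anywhere.

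On the role of the ASHAs, the visit schedule section says: "All the screen positive subjects were followed by ASHAs which is available in the ASHA follow up data". Under Data selection criteria, the default baseline comes from ASHA screening and the post-intervention data from study interviewers. The section on referral has ASHAs sending subjects to PHC doctors.

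**The concern.** The paired t-test and McNemar's test are valid if one subject's change tells nothing about another's. Two features of the plan make that doubtful.

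First, the rater changes. A stable ASHA or village level would cancel in a within-person difference if the same rater scored both times. Here an ASHA who tends to score high or low shifts the baseline of all the subjects she screened, and the interviewer's later score does not remove that shift. It stays in the change score as a component those subjects share.

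Second, the intervention reaches subjects through ASHAs and PHC doctors. How well an ASHA follows up and refers, and how accessible the PHC is, will affect the subjects they serve in similar ways. This bears most directly on service use.

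If the correlation of change within clusters is positive, the naive standard errors are too small, and the p-values in Tables 8a, 8b and 15 overstate the evidence for an effect of the intervention.

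**Working it through.** **Inputs.** The SAP states no sample size, number of ASHAs or PHCs, cluster size or ICC, so there is no figure to reproduce. Everything below is a sensitivity range on assumed values: m screen positives per ASHA, and the ICC of the change score (not of the score itself, because stable levels cancel).

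**Paired t-test.** Design effect DE = 1 + (m − 1) × ICC. The true standard error is √DE times the naive one. The actual two-sided error at nominal 5% is 2 × [1 − Φ(1.96/√DE)].

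| m | ICC | DE | √DE | Actual error |
|---|---|---|---|---|
| any | 0 | 1.00 | 1.00 | 0.050 |
| 5 | 0.01 | 1 + 4 × 0.01 = 1.04 | 1.02 | 0.055 |
| 10 | 0.02 | 1 + 9 × 0.02 = 1.18 | 1.09 | 0.071 |
| 10 | 0.05 | 1 + 9 × 0.05 = 1.45 | 1.20 | 0.104 |
| 20 | 0.02 | 1 + 19 × 0.02 = 1.38 | 1.17 | 0.095 |
| 20 | 0.05 | 1 + 19 × 0.05 = 1.95 | 1.40 | 0.160 |
| 40 | 0.05 | 1 + 39 × 0.05 = 2.95 | 1.72 | 0.254 |

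At m = 20 and ICC 0.05, a naive p of 0.01 (z = 2.576) becomes 2 × [1 − Φ(2.576/1.396)], about 0.065.

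A simulation with 40 clusters, m = 20 and 4,000 runs agrees: rejection rates of 0.050, 0.094, 0.171 and 0.253 at ICC 0, 0.02, 0.05 and 0.10.

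**McNemar's test.** Only discordant pairs count, so the effective cluster is smaller. The same set-up, with 30% of pairs assumed discordant, gave 0.047, 0.063, 0.082 and 0.121 at correlations 0, 0.02, 0.05 and 0.10 in the direction of change. A rough check at 0.05: 20 × 0.30 = 6 discordant pairs per ASHA, DE ≈ 1 + 5 × 0.05 = 1.25, and 2 × [1 − Φ(1.96/√1.25)] ≈ 0.080.

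**Case-control t-test.** The formula above does not carry over, because a case and a control may share an ASHA and the shared effect then partly cancels. Simulated error at m = 20 and ICC 0.10:

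- cases and controls equally split within each ASHA: 0.043;
- randomly mixed: 0.050;
- case share varying between ASHAs: 0.095;
- cases and controls under entirely separate ASHAs: 0.260.

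The naive test can thus be slightly conservative, about right, or too liberal. Case status is set by the ASHA's own screening result, so a case share that varies between ASHAs is plausible, but the SAP does not show it.

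**The case against.** The strongest reply is that the SAP never establishes the clusters. It says that subjects were followed by ASHAs, not that each had one particular ASHA, and it gives no cluster size or ICC. With few positives per ASHA and a small ICC of change, the error is 5.5% rather than 5%, which nobody would act on. Where an interviewer baseline is used instead of the ASHA's, the change of rater also disappears and only the delivery effect remains. All of this stands. It limits what can be said about size, but it does not make independence a safe default.

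A reader might also infer more than the document supports:

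- *That every subject was treated by a PHC doctor.* Table 17 has a row that reads "Out of those referred to PHC doctors Proportion of subjects actually visited doctors", so only some of those referred were seen. PHC clustering through treatment is partial.
- *That all the primary tests err towards low p-values.* This does not follow for the case-control tests, as the simulations show.
- *That the paired t-test range applies to service use.* At m = 20 and correlation 0.05, McNemar's simulated error was about half as large (0.082 against 0.171).
- *That the planned confidence intervals are too narrow.* For these endpoints the SAP plans p-values and no intervals.
- *That allowing for clustering also repairs the case-control contrast.* Groups defined by ASHA scoring raise a question of bias, which no variance correction removes.

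**Conclusion.** The point holds for the before-after tests. The paired t-test and McNemar's test ignore a plausible correlation of change within ASHA or PHC, and a positive correlation makes their p-values too low. The choice of test is the SAP's own business, so this is not a matter left to the protocol.

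The size cannot be fixed from the document. It rests on assumed cluster sizes of 5 to 40 and ICCs of 0.01 to 0.05, which span a negligible effect and a fivefold excess of false positives (0.254/0.05 ≈ 5) for the paired t-test. For the case-control tests the conclusion is weaker: the naive p-value is unreliable, in a direction that depends on how cases and controls are spread over ASHAs. That one ASHA serves each subject is an inference.

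**What to change.** Keep the planned point estimates (mean change, difference in proportions, difference of differences) and change how their uncertainty is computed:

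- State the cluster unit: the ASHA, or the PHC or village if that is the higher level and has enough units.
- Score change: an intercept-only linear model for the individual change, with cluster-robust standard errors.
- Service use before and after: GEE (an identity link keeps the difference in proportions) or a clustered McNemar test.
- Case-control contrasts: the same differences, with cluster-robust standard errors.
- Use a small-sample correction if clusters are few, and report 95% confidence intervals beside the p-values.
- Report the number of clusters, their sizes and the estimated ICC of change, so that readers can see whether the correction mattered.

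This change calls for no baseline adjustment, which would alter the case-control estimate.

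The cost is an ASHA or PHC identifier for each subject, presumably held with the screening data though the SAP does not say so, and a change of procedure. Intervals may be wider than naive ones, by up to about 1.7 times under the larger assumed values. If the ICC is near zero, the results will hardly move.

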#### **Demographic and Socioeconomic characteristics:**

The count and frequency for the Social characteristic like Gender, occupation, education and marital status will be presented. Age will be summarized by mean SD and range. The occupation and education was not collected at post intervention. Hence the record from baseline will be taken to post intervention for occupation and education.

### **Statistical Analysis of KAB and BACE:**

For every question related to KAB and BACE, the count and percentage will be presented for every response for the concern question.

Further to that for every question, mean score and SD along with number of people responded to different questions of KAB and BACE will be presented. The difference in score between baseline and post intervention will also be analysed by t-test. The mean SD and the number of people responded at both visit along with p-value will be presented.

For KAB the Total Behaviors SCORE (Except First Question) and For BACE, the Total BACE Score, will also be analyzed and summarized in similar fashion.

A separate table for BACE will be presented for % reporting barrier to any degree and % reporting as a major barrier along with their rank for highest proportion rating as a major barrier. The difference in proportion for %reported a major barrier will be analysed by two- proportion z-test and corresponding p-value will be presented.

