**Data selection criteria for Analysis:**

Unless otherwise stated, for baseline we have to use ASHA screening (ASHA screening 1 and ASHA follow-up 1) data. At post intervention we have to use Post intervention data collected by study interviewers linked with patient ID of ASHA screen positive data.

For certain tables the information at baseline may not be collected by ASHA during their screening. For all such instance, Baseline data collected by study interviewers will be used linked with patient ID of ASHA screen positive data.

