| Not wanting a mental health problem to be on my medical records                                             | xx, xx.xx(xx.xxx)       | xx, xx.xx(xx.xxx)                | xx, xx.xx(xx.xxx) 0.xxxx                          |
| Concern that my children may be taken in to care or that I may lose access
or custody without my consent | xx, xx.xx(xx.xxx)       | xx, xx.xx(xx.xxx)                | xx, xx.xx(xx.xxx) 0.xxxx                          |
| Concern about what my friends might think, say or do                                                        | xx, xx.xx(xx.xxx)       | xx, xx.xx(xx.xxx)                | xx, xx.xx(xx.xxx) 0.xxxx                          |
| Concern about what people at work might think, say or do                                                    | xx, xx.xx(xx.xxx)       | xx, xx.xx(xx.xxx)                | xx, xx.xx(xx.xxx) 0.xxxx                          |
| Overall BACE score                                                                                          | xx, xx.xx(xx.xxx)       | xx, xx.xx(xx.xxx)                | xx, xx.xx(xx.xxx) 0.xxxx                          |

*\*P value is calculated using t-test. BACE=barrier to access care evaluation-Treatment Stigma Subscale. For mean of difference, Subject who have responded to both the visit, have been considered for summary.*

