**Table 6: Percentage reporting and ranks for each barrier in the BACE ASHA screen positive**

| Question                                                                                                | -----Baseline-----                     |                                           |             | -----Post Intervention-----            |                                           |             | * P-Value
Visit 2-3 |
|---------------------------------------------------------------------------------------------------------|----------------------------------------|-------------------------------------------|-------------|----------------------------------------|-------------------------------------------|-------------|------------------------|
|                                                                                                         | %reporting
barrier to
any degree | %reporting as
major
barrier (a lot) | ***
Rank | %reporting
barrier to
any degree | %reporting as
major
barrier (a lot) | ***
Rank |                        |
| Concern that I might be seen as weak for having a mental health problem                                 | xx.xx                                  | xx.xx                                     | x           | xx.xx                                  | xx.xx                                     | x           | 0.xxx                  |
| Concern that it might harm my chances when applying for jobs                                            | xx.xx                                  | xx.xx                                     | x           | xx.xx                                  | xx.xx                                     | x           | 0.xxx                  |
| Concern about what my family might think, say, do or feel                                               | xx.xx                                  | xx.xx                                     | x           | xx.xx                                  | xx.xx                                     | x           | 0.xxx                  |
| Feeling embarrassed or ashamed                                                                          | xx.xx                                  | xx.xx                                     | x           | xx.xx                                  | xx.xx                                     | x           | 0.xxx                  |

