| Concern about what people at work might think, say or do                                                | xx.xx                                  | xx.xx                                     | x           | xx.xx                                  | xx.xx                                     | x           | 0.xxx                  |
| Overall Mean                                                                                            | xx.xx                                  | xx.xx                                     | x           | xx.xx                                  | xx.xx                                     | x           | 0.xxx                  |

\* *P-value calculated based on difference in proportion reported as major barrier.*

\*\*\* *Rank (1=item has highest proportion rating as a major barrier)*

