| Did you take medicines as prescribed by the primary care doctor on a regular basis? | xx(xx.xx)                |

*N=Total no. of patients in Baseline; n=No. of patients in particular category*

Table 15: Summary of for Utilization of Health Services for Screen Positive subjects

| Screen Positive | Health Service used ** | Baseline
(N=xxxxx)
n (%) | Post Intervention
(N=xxxxx)
n (%) | P-value |
|-----------------|------------------------|--------------------------------|-----------------------------------------|---------|
| By ASHA         | Yes                    | xxx (xx.xx)                    | xxx (xx.xx)                             | 0.xxxx  |
|                 | No                     | xxx (xx.xx)                    | xxx (xx.xx)                             |         |
| By Interviewer* | No                     | xxx (xx.xx)                    | xxx (xx.xx)                             | 0.xxxx  |
|                 | Yes                    | xxx (xx.xx)                    | xxx (xx.xx)                             |         |

\* This includes only those patients who were screen positive by Study Interviewer but not by ASHA.

\*\* Health Service used: At baseline: Response from the question "Did you get treated for that mental disorder?"

At Post Intervention: Response from the question "Did you get treated for your mental health condition as indicated by ASHA/Interviewer?"

P-Value is calculated based on Mc-nimar test for matched pair test of proportion.

Table 16a: Case control analysis of Change in Depression/Anxiety Score from Baseline to Post Intervention for those who had a score  $\geq 10$  at the beginning of the intervention.

| Category   | Type    | Statistics | Baseline     | Post Intervention | Change       | P-Value for difference |
|------------|---------|------------|--------------|-------------------|--------------|------------------------|
| Anxiety    | Cases   | N          | xxxxx        | xxxxx             | xxxxx        | 0.xxxx                 |
|            |         | Mean (SD)  | xx.x (xx.xx) | xx.x (xx.xx)      | xx.x (xx.xx) |                        |
|            |         | Median     | xx.x         | xx.x              | xx.x         |                        |
|            |         | Min, Max   | xx; xx       | xx; xx            | xx; xx       |                        |
|            | Control | N          | xxxxx        | xxxxx             | xxxxx        |                        |

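### Table 6 compares paired BACE 'major barrier' percentages with an unpaired two-proportion z-test, so the item p-values are not valid and are probably too large; the named test does not fit the 'Overall Mean' row at all

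*SAP*

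**What the plan says.** The SAP section on KAB and BACE fixes the method for Table 6: "The difference in proportion for %reported a major barrier will be analysed by two- proportion z-test". The table's footnote repeats the target: "P-value calculated based on difference in proportion reported as major barrier". The shell has one p-value for each of the 12 barriers and one more for a row labelled 'Overall Mean'.

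The title restricts both column blocks to one population: "Table 6: Percentage reporting and ranks for each barrier in the BACE ASHA screen positive". The section on data selection describes how records are joined. For follow-up: "At post intervention we have to use Post intervention data collected by study interviewers linked with patient ID of ASHA screen positive data". For items that the ASHAs did not collect at screening: "Baseline data collected by study interviewers will be used linked with patient ID of ASHA screen positive data". For mean change on the same BACE items, the Table 5 footnote says: "Subject who have responded to both the visit, have been considered for summary".

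Elsewhere the SAP uses paired tests for the same two time points. Table 15 (service use) states: "P-Value is calculated based on Mc-nimar test for matched pair test of proportion". For anxiety and depression scores: "The mean difference in score between baseline and post intervention will be statistically analyzed by paired t-test".

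**The concern.** A two-proportion z-test takes the variance of the difference to be the sum of two independent binomial variances. When the same person answers the same item twice, the covariance of the two answers must be subtracted. The z-test leaves it out. If the correlation is positive, the standard error is too large, the p-value is too large, and a real fall in a barrier is more easily missed.

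The 'Overall Mean' row raises a separate problem. It averages 12 item percentages, so it has no count of subjects with and without an event. Neither the z-test nor McNemar's test applies to it directly, and the SAP does not say how its p-value is obtained.

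At stake is the reading of Table 6: which stigma barriers are reported to have changed after the intervention.

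**Working it through.** **Are the samples paired?** Both column blocks of Table 6 concern ASHA screen positives. Follow-up and interviewer baseline records are joined to those subjects by patient ID, and Table 5 computes within-subject change on the same items. The two columns therefore hold repeated answers from the same people, at least in part. Nothing in the SAP calls them independent or gives a reason for an unpaired test.

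**Figures in the plan.** There are none to reproduce: the shells hold placeholders only, with no n, rate or correlation. All inputs below are assumptions.

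**True size of the z-test.** Let p be the common proportion, n the number answering at each visit, ρ the within-person correlation of the yes/no answer, and w the share of subjects who answer at both visits.
- Variance used by the z-test under no change: 2p(1−p)/n.
- Actual variance: 2p(1−p)(1−wρ)/n.
- True two-sided size of a nominal 5% test: 2[1 − Φ(1.96/√(1−wρ))].

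| Overlap w | ρ | 1.96/√(1−wρ) | True size |
|---|---|---|---|
| any | 0 | 1.96 | 5.0% |
| 100% | 0.2 | 2.19 | 2.8% |
| 100% | 0.4 | 2.53 | 1.1% |
| 50% | 0.2 | 2.07 | 3.9% |
| 50% | 0.4 | 2.19 | 2.8% |

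A negative correlation would reverse the direction: at ρ = −0.1 with full overlap, 1.96/√1.1 = 1.87 and the size is 6.2%.

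**Effect on one p-value.** Assume 200 complete pairs, with 20% rating an item a major barrier at baseline and 13% afterwards.
- z-test: pooled proportion 0.165; SE = √(2 × 0.165 × 0.835/200) = 0.0371; z = 0.07/0.0371 = 1.89; p = 0.059, whatever the pairing.
- McNemar: the share saying yes twice is p11 = 0.20 × 0.13 + ρ√(0.20 × 0.80 × 0.13 × 0.87). The discordant counts are b = 200(0.20 − p11) and c = 200(0.13 − p11), and z = (b − c)/√(b + c).
  - ρ = 0.2: p11 = 0.0529, b = 29.4, c = 15.4, z = 14/√44.8 = 2.09, p = 0.037.
  - ρ = 0.4: p11 = 0.0798, b = 24.0, c = 10.0, z = 14/√34.1 = 2.40, p = 0.016.

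This example lies close to 0.05 by construction. It shows that the choice of test can change a conclusion, not that it will.

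**Power.** For an assumed 20% v 15% in 400 pairs, the z-test has power of about 0.45 at ρ = 0.3, against 0.60 for McNemar. At ρ = 0.5 the figures are 0.44 and 0.74.

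**The case against.** **Overlap may be partial.** The both-visits footnote belongs to Table 5 and governs only its mean differences. Table 6 has no such restriction and prints no N, NA is an allowed answer, and separate post-stigma records are appended to the follow-up data. This stands. It shrinks the error, as the 50% rows show, but removes it only if hardly anyone answers twice, which does not fit the ID linkage.

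**The error is on the safe side.** This also stands for the item rows. With positive correlation the test is conservative, and near zero correlation it is about right. A reader might infer that every p-value in Table 6 is wrong, or that no item is tested at 5%. The documents do not support that, because they say nothing about correlation or overlap. Item-level false positives would need negative correlation between a person's two answers, and nothing in the SAP suggests it.

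**The overall row.** A reader might infer a badly inflated error rate, on the thought that all 12n responses will be pooled as independent. The SAP states no such method, so any figure for that inflation would be hypothetical. What holds is that a p-value is promised for a quantity to which the named test does not apply.

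**Importance.** BACE lies outside the stated primary objective (anxiety and depression scores and service use), and Table 5 tests the same items as mean scores. This limits the weight of the point. It gives no reason to keep an unpaired test.

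**Conclusion.** The point holds in a limited form. The SAP names an unpaired test for before/after percentages in linked subjects and departs, without explanation, from the paired tests it uses for service use and for symptom scores. The likely consequence for the 12 item rows is p-values that are too large, and lost power. On assumed correlations of 0.2 to 0.4, the true size of a 5% test is 2.8% to 1.1% with full overlap and 3.9% to 2.8% with half overlap. It is about 5% only if correlation or overlap is near zero. The direction rests on positive within-person correlation, which is expected of repeated answers but not documented. For the 'Overall Mean' row the named test does not apply, and the documents do not allow the size of the error to be stated. The change should be made. It concerns a secondary table and leaves the primary analysis untouched.

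**What to change.** In the KAB and BACE section and in the Table 6 footnote:
- Replace the z-test with McNemar's test, exact where discordant pairs are few, on subjects with an applicable answer to the item at both visits (NA excluded).
- Print that N for each item. Show the percentages for the paired set, or beside the all-responder percentages, so that the displayed figures match the tested set.
- Report the paired difference with a 95% confidence interval.
- For the overall row, drop the p-value. Alternatively, compute each subject's share of applicable items rated 'a lot' at each visit, apply a paired test to the difference, and relabel the row, since this is a different quantity from a mean of item percentages.

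The cost is a change of wording and a few lines of code; no new data are needed, as the records are already linked. The drawback is that subjects with only one visit leave the test. If that loss matters, a logistic GEE model clustered on subject keeps all responders and still allows for the correlation.
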